# Electrically guided versus imaging-guided implant of the left ventricular lead in cardiac resynchronization therapy: a study protocol for a double-blinded randomized controlled clinical trial (ElectroCRT)

**DOI:** 10.1186/s13063-018-2930-y

**Published:** 2018-11-01

**Keywords:** Heart failure, Cardiac resynchronization therapy, CRT, Left ventricular ejection fraction, LVEF, Electrical mapping, QLV, Cardiac imaging, Left ventricular lead placement

## Abstract

**Background:**

Cardiac resynchronization therapy (CRT) is an established treatment in patients with heart failure and prolonged QRS duration where a biventricular pacemaker is implanted to achieve faster activation and more synchronous contraction of the left ventricle (LV). Despite the convincing effect of CRT, 30–40% of patients do not respond. Among the most important correctable causes of non-response to CRT is non-optimal LV lead position.

**Methods:**

We will enroll 122 patients in this patient-blinded and assessor-blinded, randomized, clinical trial aiming to investigate if implanting the LV lead guided by electrical mapping towards the latest LV activation as compared with imaging-guided implantation, causes an excess increase in left ventricular (LV) ejection fraction (LVEF). The patients are randomly assigned to either the intervention group: preceded by cardiac computed tomography of the cardiac venous anatomy, the LV lead is placed according to the latest LV activation in the coronary sinus (CS) branches identified by systematic electrical mapping of the CS at implantation and post-implant optimization of the interventricular pacing delay; or patients are assigned to the control group: placement of the LV lead guided by cardiac imaging. The LV lead is targeted towards the latest mechanical LV activation as identified by echocardiography and outside myocardial scar as identified by myocardial perfusion (MP) imaging. The primary endpoint is change in LVEF at 6-month follow up (6MFU) as compared with baseline measured by two-dimensional echocardiography. Secondary endpoints include relative percentage reduction in LV end-systolic volume, all-cause mortality, hospitalization for heart failure, and a clinical combined endpoint of response to CRT at 6MFU defined as the patient being alive, not hospitalized for heart failure, and experiencing improvement in NYHA functional class or/and > 10% increase in 6-minute walk test.

**Discussion:**

We assume an absolute increase in LVEF of 12% in the intervention group versus 8% in the control group. If an excess increase in LVEF can be achieved by LV lead implantation guided by electrical mapping, this study supports the conduct of larger trials investigating the impact of this strategy for LV-lead implantation on clinical outcomes in patients treated with CRT.

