To clarify the potential value of an electrically guided strategy for optimizing CRT response, we designed a prospective, double-blinded, randomized trial comparing an electrically guided CRT strategy with an imaging-guided approach. We hypothesize that an electrically guided CRT strategy improves CRT response by optimal electrical resynchronization targeting LV lead placement towards the region with the latest electrical activation combined with VVd optimization to achieve the narrowest biventricular paced QRS. The aim of the present study is to investigate if this strategy of optimal electrical resynchronization causes an excess improvement in LV ejection fraction (LVEF) as compared with an imaging-guided strategy positioning the LV lead according to the latest mechanically activated non-scarred myocardial segment.

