**Fig. 4 Fig4:**
[figure not shown]
SPIRIT figure of the ElectroCRT study protocol. ECG, electrocardiogram; NYHA, New York Heart Association; MLHFQ, Minnesota Living with Heart Failure Questionnaire; 6MWT, 6-minute walk test; Rb-PET MP, rubidium positron emission tomography myocardial perfusion imaging; CT, computed tomography; VV, interventricular; AV, atrioventricular; LV, left ventricular; LVEF, left ventricular ejection fraction; LVESV, left ventricular end-systolic volume, CRT, cardiac resynchronization therapy; 6MFU, 6-month follow up; QoL, quality of life; Nt Pro-BNP, N-terminal prohormone of brain natriuretic peptide, LVEDV, left ventricular end-diastolic volume

Immediately after the implantation, the VVd settings are programmed by the physician performing the implantation, to obtain the narrowest QRS width. This is performed by measuring QRS width as the maximal QRS duration in any lead in the 12-lead ECG recorded at five different VVd settings: (1) right ventricle (RV) stimulation 20 ms prior to LV stimulation, (2) simultaneous biventricular pacing, (3) LV stimulation 20 ms prior to RV stimulation, (4) LV stimulation 40 ms prior to RV stimulation, and (5) LV stimulation 60 ms prior to RV stimulation.

Control group: prior to implantation the fluoroscopic venography is co-registered to the CT venography to visualize available CS branches. After combining information from echocardiography, Rb-PET, and cardiac CT, the LV electrode is targeted towards the CS branch closest to the latest mechanically activated non-scarred myocardial segment. Basal and mid-LV segments of the CS tributaries are prioritized separately according to the relation with basal and mid-LV segmental mechanical activation delay. CT images of cardiac venous anatomy are available to the physician performing the implantation in a 2D short-axis view and in 3D volume-rendered reconstructions. The CS tributary closest to the optimal LV pacing site is labeled as first priority for LV lead placement. Tributaries closest to the second, third, or fourth latest activated segment with viable myocardium are chosen as the second, third, or fourth priority [17].

In the imaging group, the VVd is programmed to simultaneous biventricular stimulation. In both treatment groups, atrioventricular (AV) optimization is performed the day after implantation using the iterative method ensuring maximal separation of the E-wave and A-wave without termination of the A-wave [27].

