### Perspective

No randomized trial has investigated the effect of a CRT implant-strategy targeting optimal electrical resynchronization achieved by guiding LV lead placement to the myocardial region with the latest electrical activation combined with post-implant VVd optimization for narrowing the paced QRS width. If an excess increase in LVEF is achieved by LV lead implantation guided by systematic electrical mapping followed by VVd optimization for narrowing paced QRS, this study supports the conduct of larger, multicenter, randomized clinical trials investigating the impact of electrically guided LV lead implantation on clinical outcomes in patients treated with CRT.

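### The abstract's aim and conclusion, and the closing future-trials clause, name electrically guided lead implantation alone, although the arms also differ in VVd programming and the main-text aim is the combined strategy

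*Protocol article*

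**What the plan says.** All places are in the protocol article.

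- **Abstract, Methods (aim).** The trial is described as "aiming to investigate if implanting the LV lead guided by electrical mapping towards the latest LV activation as compared with imaging-guided implantation" leads to a larger rise in LVEF. VVd is not part of that statement. The description of the intervention arm that follows does list "post-implant optimization of the interventricular pacing delay". The abstract does not give the control arm's VVd setting.
- **Abstract, Discussion (conclusion).** "If an excess increase in LVEF can be achieved by LV lead implantation guided by electrical mapping, this study supports the conduct of larger trials". VVd is not named.
- **Background (hypothesis and aim).** Lead placement at the latest electrical activation is "combined with VVd optimization to achieve the narrowest biventricular paced QRS", and the aim refers to that whole strategy.
- **Methods, The applied strategies for cardiac resynchronization therapy.** In the intervention arm QRS width is measured at five VVd settings, and "the VVd settings are programmed by the physician performing the implantation, to obtain the narrowest QRS width". For the control arm: "In the imaging group, the VVd is programmed to simultaneous biventricular stimulation". Study design describes the arms in the same way. Atrioventricular optimization is common to both: "In both treatment groups, atrioventricular (AV) optimization is performed the day after implantation".
- **Discussion, Perspective.** The condition for a positive conclusion names mapping-guided implantation followed by VVd optimization. The larger trials that should follow are then described as "investigating the impact of electrically guided LV lead implantation on clinical outcomes in patients treated with CRT", without VVd.

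**The concern.** The abstract asks a causal question about one component and draws its conclusion about that component, while the randomized contrast changes two. The article itself treats the second as potentially effective. The Background lists device programming beside lead position as a correctable cause of non-response and cites work suggesting that QRS-based VVd programming raises response. The Discussion section on the electrically guided strategy repeats this.

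If LVEF improves more in the intervention arm, a reader who follows the abstract will credit the lead site. The gain could come partly or wholly from programming, which is a separate step carried out after the lead is in place. The follow-on trials, as described in the abstract and in the last clause of the Perspective, would then be aimed at a component whose own effect this trial has not shown.

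**Working it through.** **1. The plan's own figure.** Inputs from Sample size: difference 4 points (12% versus 8%), SD 7%, two-sided alpha 0.05, power 80%, allocation 1:1.

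n per arm = 2 × (1.960 + 0.842)² × 7² / 4² = 2 × 7.851 × 49 / 16 ≈ 48.1, rounded up to 49, so 98 in total. This matches the stated 98. The t-based solution is 49.05 per arm. The 4 points are assumed for the intervention strategy as a whole; no separate lead or VVd effect is given.

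**2. What the arm difference estimates.** Let L = 1 if the lead is placed by electrical mapping and 0 if by imaging. Let V = 1 if VVd is programmed to the narrowest QRS and 0 if it is fixed at simultaneous pacing. Write the mean LVEF change as

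μ + λL + νV + ιLV.

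| Arm | L | V | Mean change |
|---|---|---|---|
| Intervention | 1 | 1 | μ + λ + ν + ι |
| Control | 0 | 0 | μ |

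Difference = λ + ν + ι. The two mixed cells are not studied, so there is one estimable quantity for three unknowns. Atrioventricular optimization is the same in both arms and adds no further term.

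**3. Sample size and adjustment do not help.** With 58 evaluable per arm (116 / 2), the standard error of the difference is 7 × √(2/58) = 1.30 points. More patients shrink this, but what is estimated remains the sum. The planned covariates (etiology, baseline LVEF, sex, baseline QRS width) do not help either, because the assigned VVd rule coincides exactly with the arm.

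**4. Illustration, by assumption only.** Take the planned total of 4 points and no interaction:

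| Assumed VVd part | Lead part | Arm difference | Power at 58 per arm |
|---|---|---|---|
| 0 | 4 | 4 | 87% |
| 2 | 2 | 4 | 87% |
| 4 | 0 | 4 | 87% |

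The three rows cannot be told apart from the trial's result. The lead part could lie anywhere from 0 to all of the 4 points, and the article gives nothing with which to narrow that range.

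**5. The statements side by side.**

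| Place | Lead placement named | VVd optimization named |
|---|---|---|
| Abstract, aim | yes | no |
| Abstract, description of the intervention arm | yes | yes |
| Abstract, conclusion | yes | no |
| Background, hypothesis and aim | yes | yes |
| Perspective, condition | yes | yes |
| Perspective, future trials | yes | no |

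Three statements name one component. The rest, and the design, name both. The Limitations section covers the single center, image alignment and radiation, but not the inability to separate the two components.

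**The case against.** The bundle is deliberate and openly declared. The Background names the combination as the open question, Study design lists both components, and the Discussion speaks of a combined optimization strategy. The sample size is set for the strategy. A two-arm comparison of strategies is legitimate, and no such comparison isolates components. The abstract's aim can be read as shorthand, since VVd optimization appears in its description of the intervention arm. Choice of endpoint also calls the findings hypothesis-generating.

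Most of this stands, and it rules out several stronger readings that a reader might reach:

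- *That the trial cannot answer its question.* It can answer the one in the Background.
- *That the Perspective also credits the gain to lead placement alone.* Its condition names VVd optimization; only its description of the next trials omits it.
- *That every intervention patient received different programming.* Simultaneous pacing is one of the five settings tested, so some patients may end with the control arm's setting.
- *That the chance of a misattributed positive result can be calculated.* Any VVd-only effect put into a power formula would be invented. The result would be ordinary power for a difference of that size, not a measure of misattribution.
- *That a null result would conceal opposing effects.* The algebra allows it, but nothing in the article suggests it.

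The defence does not remove the mismatch itself. Shorthand is harmless in a description. It is not harmless in a conclusion that says what achieved the gain and what should be tested next.

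**Conclusion.** The point holds as a fault of stated aim and attribution. The abstract's aim, the abstract's conclusion and the future-trials clause of the Perspective claim, or pass on, a lead-placement effect that the two-arm design cannot identify, and they differ from the main-text aim. The difference between arms supports a statement about the combined strategy only.

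No magnitude can be assigned, because the article gives no split between the components. The conclusion rests on two things in the text: VVd is handled by a different rule in each arm, and the article itself regards VVd optimization as possibly effective. Design, primary endpoint, sample size and primary analysis stand. The correction is worth making because the abstract is where the trial's claim will most often be read.

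**What to change.** 1. Reword the abstract's aim and conclusion and the last clause of the Perspective to match the Background: electrically guided lead placement plus QRS-based VVd optimization, compared with imaging-guided placement with simultaneous biventricular pacing.
2. Add one sentence to the Limitations: the two components were changed together, so a difference in LVEF cannot be attributed to lead placement alone.
3. Describe the VVd settings selected in the intervention arm. Randomization and blinding procedures states that optimization data are entered in the case record form, so nothing new need be collected. Keep this descriptive: patients left at simultaneous pacing are selected after randomization, and comparing them with the control arm would not be a randomized comparison of lead placement.

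The article reports enrollment as complete, so these are changes of wording and reporting, to be carried into the results report as well. They alter no treatment, endpoint, sample size or analysis. The cost is a few sentences, one descriptive table and a narrower claim.

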**Trial registration:**

ClinicalTrials.gov, NCT02346097. Registered on 12 January 2015.

Patients were enrolled between 16 February 2015 and 13 December 2017.

**Electronic supplementary material:**

The online version of this article (10.1186/s13063-018-2930-y) contains supplementary material, which is available to authorized users.

## Background

Cardiac resynchronization therapy (CRT) improves survival, symptoms, and left ventricular (LV) function in patients with medical refractory heart failure and prolonged QRS duration [1–4]. Nevertheless, 30–40% of the patients experience no clinical benefit and the associated risk of complications is non-negligible [5–7].

Potentially correctable causes of non-response to CRT are LV lead positioning and device programming [7, 8]. Guidelines recommend positioning of the LV lead in non-scarred, non-apical, and postero-lateral myocardial segments with late electrical activation [1]. Recent randomized controlled trials have demonstrated improved response to CRT when applying an imaging-guided LV lead placement strategy targeting the latest mechanically activated, non-scarred, myocardial segment, compared with standard care [9–11]. However, imaging-guided strategies are time-consuming, costly, and difficult to align with fluoroscopic imaging during device implantation.

An alternative approach for individualized LV lead placement is to target the myocardial region with the latest electrical activation; a strategy with the advantage of electrical measurements being immediately available during the implant procedure. Retrospective studies have documented an association between pacing the LV in a region with late electrical activation and improved outcome after CRT [12, 13]. However, these studies did not perform systematic electrical activation mapping or evaluate the influence of myocardial scar tissue.

Recently, electrical resynchronization with narrowing of the QRS width during CRT has been associated with better outcome [14]. Furthermore, programming of the interventricular pacing delay (VVd) to achieve the shortest QRS duration is suggested to increase CRT response [15, 16]. Whether the outcome of CRT is improved when combining electrically guided LV lead placement and optimizing the VVd to achieve the shortest QRS duration is unknown.

To clarify the potential value of an electrically guided strategy for optimizing CRT response, we designed a prospective, double-blinded, randomized trial comparing an electrically guided CRT strategy with an imaging-guided approach. We hypothesize that an electrically guided CRT strategy improves CRT response by optimal electrical resynchronization targeting LV lead placement towards the region with the latest electrical activation combined with VVd optimization to achieve the narrowest biventricular paced QRS. The aim of the present study is to investigate if this strategy of optimal electrical resynchronization causes an excess improvement in LV ejection fraction (LVEF) as compared with an imaging-guided strategy positioning the LV lead according to the latest mechanically activated non-scarred myocardial segment.

## Methods

### Study design

The Electrically versus Imaging-guided Implant of the Left Ventricular Lead in Cardiac Resynchronization Therapy Study (ElectroCRT) is a prospective, patient-blinded and assessor-blinded, single-center, randomized, controlled trial. Study participants are allocated 1:1 to either the intervention group or the control group as follows:Intervention group (electrically guided) including pre-implant cardiac computed tomography (CT) to visualize cardiac venous anatomy, procedural electrical activation mapping of all available coronary sinus (CS) branches, placement of the LV lead to pace the site of latest electrical activation, and procedural VVd optimization to achieve the shortest possible QRS duration.Control group (imaging-guided) including pre-implant cardiac CT to visualize cardiac venous anatomy, speckle-tracking echocardiography to identify the LV myocardial segment with the latest mechanical activation, and myocardial perfusion (MP) imaging (^82^Rubidium positron emission tomography (Rb-PET)) to localize the LV myocardial scar. The LV lead is targeted towards the CS branch closest to the latest mechanically activated non-scarred segment and simultaneous biventricular stimulation is applied [17].

One day prior to implantation, all patients undergo identical pre-implant clinical evaluation and imaging acquisition after providing written informed consent. Patients are followed for 6 months. The study course is illustrated in Figs. 1 and 2.

**Fig. 1 Fig1:**
[figure not shown]
Consort diagram of the study course. 6MWT, 6-minute walk test; AV, atrioventricular; CRT, cardiac resynchronization therapy; CT, computed tomography; LV, left ventricular; LVEF, left ventricular ejection fraction; MLHFQ, Minnesota Living with Heart Failure Questionnaire; MP, myocardial perfusion; NYHA, New York Heart Association; QoL, quality of life; VVd, interventricular pacing delay

**Fig. 2 Fig2:**
[figure not shown]
Control group: pre-implant imaging obtained to guide implantation of the left ventricular (LV) lead. **a** Echocardiographic LV short-axis view of the basal (left) and mid-LV imaging plane (right) each divided into six anatomical segments. Numbers indicate time to peak radial strain in milliseconds (ms). **b** Baseline cardiac computed tomography (CT) images in three-dimensional 3D reconstruction illustrating cardiac venous anatomy. Posterior (left) and lateral (right) view of LV. **c** Baseline cardiac CT image in the mid-LV multiplanar reformatted short-axis view illustrating cardiac venous anatomy. **d** Rubidium positron emission tomography (Rb-PET) myocardial perfusion (MP) imaging, LV 17-segment bulls-eye plot. Numbers indicate percentage of tracer-uptake; < 50% is considered as transmural scar tissue. AIV, anterior interventricular vein; Ant, anterior; Ant-Sept, antero-septal; CS, coronary sinus; Inf, inferior; LAD, left anterior descending artery; Lat, lateral; LMA, left marginal artery (circumflex artery branch); LMV, left marginal vein; MCV, middle cardiac vein; PDA, posterior descending artery (right coronary artery branch); PLA, posterolateral artery; Post, posterior; PV, posterior vein; RCA, right coronary artery; RV, right ventricle; Sept, septal

### Study population

Patients are recruited at a tertiary referral center (Department of Cardiology, Aarhus University Hospital, Denmark). Consecutive patients referred to CRT-pacemaker (CRT-P) or CRT-defibrillator (CRT-D) and meeting the inclusion and exclusion criteria are eligible for study participation (Table 1).

**Table 1 Tab1:** Inclusion and exclusion criteria

Inclusion criteria	
Symptomatic heart failure (NYHA class II–IV despite OMT)	
ECG with LBBB according to the Strauss criteria [37] or indwelling single or dual chamber pacemaker and a paced QRS ≥ 180 ms	
LVEF ≤ 35%	
Age ≥ 40 years	
Written informed consent	
Exclusion criteria	
Expected lifetime < 6 months	
Expected cardiac surgery within the next 6 months	
Recent (< 3 months) myocardial infarction or CABG	
Pregnant or lactating	

*NYHA* New York Heart Association, *OMT* optimal therapy for the individual patient at the time of referral for cardiac resynchronization therapy, *ECG* electrocardiogram, *LBBB* left bundle branch block, *LVEF* left ventricular ejection fraction, *CABG* coronary artery bypass graft

### Ethical considerations

The trial will be conducted according to the principles of the Helsinki Declaration II [18] and the protocol has been written in accordance with the Standard Protocol Items: Recommendation For Interventional Trials (SPIRIT) checklist (Additional file 1). The trial has been registered at ClinicalTrials.gov (identifier NCT02346097), 12 January 2015. Patients were enrolled between 16 February 2015 and 13 December 2017. The study protocol has been approved by The Central Denmark Region Committees on Health Research Ethics and by the Danish Data Protection Agency. Both implantation strategies have previously been used in clinical settings and are not known to be associated with excess risks.

